### Study setting

The study is being conducted in the Youth Mood Clinic (YMC), which is part of the Orygen Youth Health Clinical Program (OYHCP), and in associated *headspace* centres. OYHCP is a youth public mental health service for 15- to 25-year-olds who live in western metropolitan Melbourne, Australia. YMC treats about 150 patients each year, about 80% of whom have a diagnosis of MDD. The clinic is staffed by psychiatrists, psychiatry trainees and therapists, who are mainly clinical psychologists, but also include social workers and occupational therapists. Patients are reviewed regularly by their treating doctors, and therapists deliver weekly CBT and case management. All patients have access to after-hours crisis care and inpatient treatment when needed. About half of the YMC patients are being treated for depression for the first time, and comorbid diagnoses are common: 30% have comorbid anxiety disorders, and 12% have substance use disorders. The median length of treatment at the clinic is 6 months.

The *headspace* centres provide enhanced primary care services funded by the Australian government and are located throughout the country. Local centres in the northern and western regions of Melbourne are managed by the OYHCP. The *headspace* centres are staffed by psychiatrists, general practitioners and allied health professionals who manage patients between 12 and 25 years of age with high-prevalence mental illnesses, mainly depression and anxiety. The model of care is similar to that at YMC, with patients being reviewed regularly by medical practitioners and attending weekly CBT sessions with their therapists.

### Inclusion and exclusion criteria

The criteria for inclusion in and exclusion from the study are designed to reflect the real-world characteristics of the young people with depression who present to the clinical centres. The inclusion criteria are (1) age between 15 and 25 years at the time of commencement of the intervention; (2) diagnosis of MDD based on the Structured Clinical Interview for DSM-IV Axis I Disorders, Patient Edition (SCID-I/P) [45]; (3) score of 20 or higher on the MADRS, indicating depression of at least moderate severity; and (4) ability to provide written informed consent (including both adequate intellectual capacity and fluency in the English language).

The exclusion criteria are (1) lifetime or current SCID-I/P diagnosis of a psychotic disorder, (2) lifetime or current SCID-I/P diagnosis of bipolar I or II disorder, (3) acute or unstable medical disorder that would interfere with treatment, (4) current pregnancy, (5) severe disturbance such that the young person would be unable to comply with the requirements of informed consent or comply with the study protocol, (6) current treatment with an antidepressant medication taken for at least 2 weeks and (7) previous treatment with fluoxetine that was either ineffective or poorly tolerated.

### Enrolment and randomisation

After participants provide their written informed consent (which will also be obtained from a parent or legal guardian if the participant is younger than 18 years of age), they will undergo a baseline assessment in which they will be screened for eligibility. Participants will be randomised to either the CBT + FLX or CBT + PBO group in a 1:1 ratio, sequentially as they become eligible for randomisation. The randomisation will be stratified by site (OYHCP and *headspace* centres), age (≤18 and >18 years) and sex, and randomly permuted blocks (of sizes 2, 4 and 6) will be programmed into the electronic case report form by an independent statistician. The investigators, research assistants, study biostatistician, clinicians and participants will all be blinded with respect to randomisation. Only the pharmacist will be aware of the group to which the participant has been allocated. Participants can be unblinded in emergency situations when it is important that medical staff know which medication the participant has received. If unblinded, the participant’s treatment in the study will then be discontinued. Participants whose study medication treatment is discontinued will continue to be assessed at the scheduled times, provided they have not withdrawn their consent. Participants will be unblinded by the treating doctor after the 12-week period so that the doctor can make appropriate clinical decisions about the participant’s continuing management.

### Study medication

Participants will be commenced on one 20-mg tablet of fluoxetine or one tablet of the placebo pill. The medication can be increased to fluoxetine 40 mg daily (or to two placebo pills) if there is a poor clinical response at any time after the first 4 weeks. The medication will be prescribed by the treating doctor after the baseline visit is completed and the participant has been randomised. The trial medications will be supplied every 4 weeks following medical review, with a total of three dispensations per participant. Adherence to medication will be assessed by self-report and a pill count.

Participants will not be allowed to be treated with antipsychotic medications or mood-stabilising medications during the 12 weeks of the trial. They can be treated with sedative hypnotics (benzodiazepines and benzodiazepine-like medications) as clinically indicated. The use of medications for treatment of medical illnesses is permitted. During the follow-up period (between 12 and 26 weeks), which will be uncontrolled, treatments can be prescribed as clinically indicated. The administration of all medications (including investigational products) will be recorded during the 12-week trial and at the 26-week follow-up examination.

### Cognitive behavioural therapy

CBT is the most studied psychotherapy for young people with depression, with more than 30 trials in child and adolescent patients [33] and over 100 trials in adult patients [46]. Treatment manuals used in these trials have targeted either paediatric or adult populations, however, and are not especially suitable for young people ranging in age from late adolescence to young adulthood. To bridge this gap, we have developed a CBT manual for youth depression in collaboration with clinicians from YMC and the *headspace* centres. Recent evidence supports the use of ‘modular’ CBT manuals [47] encompassing a flexible and formulation-driven approach to therapy rather than the more linear approach prescribed by older treatment manuals. The manual that has been developed consists of 14 modules comprising 7 core modules and 7 targeted modules. The core modules are delivered to all participants and represent the central components of CBT. They cover psychoeducation, monitoring emotions, behavioural activation, chain analysis, identifying negative thoughts, restructuring negative thoughts and relapse prevention. The skills developed in each of the core modules can be revised and practiced over the course of several sessions. The targeted modules are used as suggested by the participant’s difficulties, such as if the participant has particular problems with insomnia or social anxiety. Thus, not every targeted module is relevant for every participant.

The therapist will record details of each of the sessions that the participant attends, including documenting the modules delivered. Weekly 50-minute sessions will be offered for 12 weeks. Participants will be expected to attend each week, but not all of the participants are likely to be able to attend every session. When possible, the therapist will attempt to reschedule sessions that the participant is unable to attend. All therapists will attend regular supervision sessions with senior clinicians. The fidelity of CBT treatment will be assessed in terms of adherence and competence. Each CBT session will be recorded, and the deidentified recording will be stored on a secure server. Random sessions from the course of therapy for each participant will be independently rated using CBT fidelity scales.

### Outcome measures

In addition to the primary outcome measure (the MADRS), we will use a number of measures to assess secondary clinical outcomes, functioning, QoL and safety.

#### Secondary clinical measures

The secondary clinical outcome measures we will use are the Quick Inventory of Depression Symptomatology–Self Report [48], the CGI Scale severity score [34], the CGI Scale improvement score [34] and the Patient Global Impression improvement score [49].

#### Functioning and quality-of-life measures

The functioning and QoL outcome measures we will use are the Social and Occupational Functioning Scale [50], the Social Adjustment Scale–Self-Report [51] and the Quality of Life Enjoyment and Satisfaction Questionnaire–Short Form [52].

#### Safety measures

Safety will be assessed using the Suicidal Ideation Questionnaire [53] and the Columbia Suicide Severity Rating Scale [54].

### Predictors, moderators and mediators of treatment response

We will explore factors that might explain individual differences in treatment outcomes. These factors will include (1) clinical variables, such as the duration of the depressive episode, the number of episodes and family history; (2) treatment variables, such as the quality of therapy and the number of therapy sessions attended; and (3) measures of personality, bipolarity and substance use. In addition, participants will have the option to provide blood samples and to undergo baseline brain imaging. For the blood sampling, 30 ml of blood will be drawn from consenting participants at baseline and at week 12, and the blood will be processed and stored for later analyses. We are particularly interested in examining inflammatory biomarkers and understanding how these might relate to treatment outcomes [10]. For imaging analysis, consenting participants will undergo a 1-hour magnetic resonance imaging session, during which they will complete a number of tasks. These tasks will include a cognitive reappraisal paradigm, an emotional face-matching task and a self-referential task. The data will be analysed to determine whether brain imaging variables could predict treatment outcomes, including whether they moderate or mediate outcomes.

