### Statistical methods and determination of sample size

Primary analyses will be undertaken on an intention-to-treat basis, including all participants as randomised, regardless of treatment actually received. The CBT + FLX group will be compared with the CBT + PBO group using a planned contrast of change from baseline to the week 12 endpoint on the basis of MADRS scores within a mixed-model repeated measures analysis [55]. Stratification variables will be evaluated and retained in analyses where they are measured as significant or quasi-significant. An unconstrained variance–covariance matrix will model within-individual dependencies. Transformation of scores, including categorisation, may be undertaken to meet distributional assumptions and accommodate outliers. Comparisons of changes in MADRS scores from baseline to other time points will be undertaken as secondary analyses.

Models for binary outcomes analogous to the primary analysis approach will be used to compare the remission rates and other dichotomous outcomes between the two treatment arms at endpoints and other occasions of measurement. Relative and absolute risk reduction, number needed to treat [56] and other relevant indices will be calculated for these outcomes. In analyses of scaled secondary variables, methods comparable to those employed in the primary analysis will be used. In exploratory analyses, the effects of moderators and mediators of treatment will be examined. Safety data will be compared between treatment arms—in particular, the rates of suicide-related adverse events—using Fisher’s exact test. All tests will be conducted using a two-sided α level of 0.05 and 95% confidence intervals.

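### Brain imaging done once, at baseline, is to be tested as a mediator of outcome, a role that a pre-treatment measurement cannot fill

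*Protocol article*

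**What the plan says.** All of the imaging plan is in the protocol article under Predictors, moderators and mediators of treatment response. Participants may choose "to undergo baseline brain imaging", and "consenting participants will undergo a 1-hour magnetic resonance imaging session, during which they will complete a number of tasks". This is one session, and no repeat scan appears anywhere in the article. The data are then to be used to establish whether "brain imaging variables could predict treatment outcomes, including whether they moderate or mediate outcomes".

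Three other statements fix the context:

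- **Blood sampling.** In the same paragraph, "30 ml of blood will be drawn from consenting participants at baseline and at week 12". Where two time points are intended, the article says so.
- **Start of treatment.** Under Study medication, the trial drug is "prescribed by the treating doctor after the baseline visit is completed and the participant has been randomised".
- **Status of the analysis.** Under Statistical methods and determination of sample size, "In exploratory analyses, the effects of moderators and mediators of treatment will be examined".

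**The concern.** Mediation asks whether treatment works through an intermediate variable. It needs a variable that allocation can change and that is measured before the outcome it is said to explain. A scan taken before the first tablet fails the first requirement, so the measurement schedule rules out one of the three uses the article gives it.

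What is at stake is how a secondary paper would be read. Mediation software will return an indirect effect for any variable supplied to it. If a baseline imaging measure happens to differ between arms and also predicts MADRS change, the output will look like a mechanism for fluoxetine when it is only chance imbalance in a prognostic variable.

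**Working it through.** The article gives no figure for this analysis, so there is nothing to reproduce. The check is one of logic, followed by an illustration.

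**Step 1: order of events.** Under Enrolment and randomisation, participants consent, have a baseline assessment, and are then randomised 1:1. Under Study medication, the drug is prescribed after both the baseline visit and randomisation. The scan is labelled baseline. The sequence is scan, allocation, treatment, outcome at week 12. I take the label at its word and assume the scan precedes the first dose; the article does not date the scan more closely.

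**Step 2: the mediation model.** Let T be the arm (1 = CBT + fluoxetine, 0 = CBT + placebo), M an imaging variable and Y the outcome:

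- M = m0 + a·T + error
- Y = y0 + c·T + b·M + error
- indirect effect = a × b

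M is fixed before T can act, and T is randomised, so a = 0. Hence a × b = 0 × b = 0 for every value of b. A strong association between M and Y (large b) makes M a good predictor. A T-by-M interaction makes it a moderator. Neither makes it a mediator.

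**Step 3: what an analysis would return.** The estimate of a varies around zero because the arms differ by chance. For M in SD units with n per arm, the standard error of a is √(2/n). With 260 participants, n = 130 and √(2/130) = 0.124. With an assumed slope b = 0.5, the indirect effect would vary with an SD of about 0.5 × 0.124 = 0.062.

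A simulation of 4000 trials with 130 per arm, a treatment effect of 0.35 and b = 0.5 (both coefficients assumed) agrees:

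| Variable | True a × b | Mean estimate |
|---|---|---|
| Measured at baseline only | 0 × 0.5 = 0 | -0.001 (SD 0.061) |
| Measured after treatment, shifted by it (assumed a = 0.5) | 0.5 × 0.5 = 0.25 | 0.249 |

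An SD of 0.061 is 0.061 / 0.35 = 17% of the simulated treatment effect. An apparent share of that size, of either sign, is therefore ordinary noise around a true value of zero. It uses every participant, which is the most favourable case. Imaging is optional, and fewer scans would make n smaller and √(2/n) larger.

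**Step 4: is treatment mediation what is meant?** The section heading refers to treatment response, and the statistical section refers to mediators of treatment. Both point to mediation of the treatment effect.

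**The case against.** The strongest defence has three parts.

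- **Another sense of the word.** Baseline imaging could be thought to mediate between some other baseline factor, such as family history, and outcome. That is a coherent question, but the heading and the statistical section both speak of treatment, so the text as written does not ask it.
- **A matter for the analysis plan.** A condensed article properly leaves the mediation model to a fuller document. That covers omitted detail. Here the article states a use that its own schedule rules out, and no analysis plan can supply a scan that was not taken.
- **Little depends on it.** This stands in full. The imaging is optional, the analysis is declared exploratory, and the primary comparison is by intention to treat. It limits the severity, but it does not make the quantity estimable.

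A reader might also infer that the same paragraph misassigns other variables. The documents do not support this.

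- **Blood.** The article says only that inflammatory biomarkers may be related to outcomes, which is association; it attaches mediation to imaging alone. A week-12 sample also precedes the week-26 assessment, although that follow-up period is uncontrolled.
- **Attendance and therapy quality.** "the quality of therapy and the number of therapy sessions attended" are listed among factors that may explain differences in outcome. They are not called moderators of the randomised effect. No analysis is stated that would condition the treatment comparison on them, so there is no ground for saying that the randomised comparison is compromised.

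**Conclusion.** The point holds for imaging, and only for imaging. As written, the article plans a mediation analysis in which the true indirect effect is zero for every imaging variable, so any positive finding would be false. This rests on three readings of the text: the scan precedes treatment, it is not repeated, and mediation refers to the effect of allocated treatment. The first two follow from the label and the single session described, the third from the heading and the statistical section.

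The size is minor and confined to exploratory work. A reader might want an overall chance of a spurious mediation finding, but the documents do not support one. They give no number of imaging variables, no test and no correlation between measures. If one assumes 20 independent variables at α = 0.05, the answer depends on the second path. If the variable-to-outcome path is always detected, it is 1 − 0.95^20 = 64%. If that path is null and both paths must be significant, it is 1 − (1 − 0.05 × 0.05)^20 = about 5%. A range that wide, resting on an assumed count, is no basis for a quoted error rate, and the conclusion does not need one.

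**What to change.** In Predictors, moderators and mediators of treatment response, remove the reference to mediation from the imaging sentence. Suitable wording would be: *Baseline imaging variables will be examined as predictors of outcome and as moderators of the effect of fluoxetine relative to placebo.*

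Add one general sentence there or in the statistical section: *Mediation analyses will use only variables measured after randomisation and before the outcome they are meant to explain.* MADRS scores at weeks 4 and 8 meet that condition for a week-12 outcome such as functioning or quality of life.

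The cost is a change of wording. The one claim given up is one that the design could not deliver. If imaging mediation is truly of interest, the alternative is a further scan after randomisation and before the outcome, which means added participant burden and expense and is not needed to correct the text.

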### Assessment of suicidal ideation and behaviours

Monitoring participants closely for the presence of suicidal thoughts and behaviours is an important component of the study protocol. Participants will be clinically assessed for the presence of suicidal ideation and behaviours at each meeting with their doctor (which will occur at least every 4 weeks) and at their weekly therapy sessions. The assessment will be carried out using a structured tool, the Columbia Suicide Severity Rating Scale [54]. In addition, participants will complete the Suicidal Ideation Questionnaire [53] at the research assessment sessions. If the young person indicates the presence of suicidal thinking in a research assessment, the research assistant will liaise with the participant’s treating doctor or therapist, and the clinician will ensure that an appropriate management plan is in place. If participation in the study interferes with appropriate clinical management of risk of harm to the individual (as adjudged by the treating clinicians), then that person’s participation in the study will be discontinued.

### Statistical methods and determination of sample size

Primary analyses will be undertaken on an intention-to-treat basis, including all participants as randomised, regardless of treatment actually received. The CBT + FLX group will be compared with the CBT + PBO group using a planned contrast of change from baseline to the week 12 endpoint on the basis of MADRS scores within a mixed-model repeated measures analysis [55]. Stratification variables will be evaluated and retained in analyses where they are measured as significant or quasi-significant. An unconstrained variance–covariance matrix will model within-individual dependencies. Transformation of scores, including categorisation, may be undertaken to meet distributional assumptions and accommodate outliers. Comparisons of changes in MADRS scores from baseline to other time points will be undertaken as secondary analyses.

Models for binary outcomes analogous to the primary analysis approach will be used to compare the remission rates and other dichotomous outcomes between the two treatment arms at endpoints and other occasions of measurement. Relative and absolute risk reduction, number needed to treat [56] and other relevant indices will be calculated for these outcomes. In analyses of scaled secondary variables, methods comparable to those employed in the primary analysis will be used. In exploratory analyses, the effects of moderators and mediators of treatment will be examined. Safety data will be compared between treatment arms—in particular, the rates of suicide-related adverse events—using Fisher’s exact test. All tests will be conducted using a two-sided α level of 0.05 and 95% confidence intervals.

The primary outcome measure is change on the MADRS at 12 weeks. On the basis of large, previously published fluoxetine trials of adolescent depression, we have estimated the pre–post effect size for fluoxetine to be 0.35. This value is less than the mean effect size of 0.5 reported in previous trials, as we have taken into account the modest effectiveness of the CBT administered in both arms. To sufficiently power the study, and assuming a correlation of 0.5 between baseline and 12-week endpoint measurements, a total sample size of 260 participants will be required. For the secondary outcome measure, remission at 12 weeks, there will be 74% power to detect an improvement in the rate of remission of at least 15% in the CBT + FLX arm, assuming remission in the CBT + PBO arm of 20% (consistent with remission in the TADS study).

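### The primary contrast on change in MADRS is valid but, as written, uses the baseline less efficiently than a baseline-adjusted model would: about 80% against 90% power if the SDs are equal, more likely a 5 to 8 point gap given the entry floor

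*Protocol article*

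**What the plan says.** All of the statistical text is in the protocol article, under Statistical methods and determination of sample size. The primary comparison is a "planned contrast of change from baseline to the week 12 endpoint on the basis of MADRS scores within a mixed-model repeated measures analysis", with an unconstrained variance–covariance matrix. The only covariates named are the stratification variables, kept if significant or nearly so. Neither a baseline MADRS term nor a shared baseline mean is mentioned. Scaled secondary outcomes are to be analysed by comparable methods.

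On sample size the same section says "we have estimated the pre–post effect size for fluoxetine to be 0.35" and, "assuming a correlation of 0.5 between baseline and 12-week endpoint measurements, a total sample size of 260 participants will be required". The test level is given as "All tests will be conducted using a two-sided α level of 0.05 and 95% confidence intervals". No figure for primary power is given; the text says only "To sufficiently power the study". Under Inclusion and exclusion criteria, entry requires a "score of 20 or higher on the MADRS".

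**The concern.** A contrast of change from baseline within a repeated-measures model naturally makes baseline one of the response occasions. If each arm has its own baseline mean and the data are complete, the week-12 contrast equals a two-sample comparison of change scores. Randomisation makes the true baseline means equal, so estimating a separate one for each arm adds noise that the design does not require. A common baseline mean, or baseline as a covariate, removes that noise and estimates the same between-arm difference.

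At a correlation of 0.5 with equal SDs, the change contrast has exactly the variance of a comparison that ignores baseline. The trial would then measure baseline MADRS in everyone and gain no precision from it. Precision matters here because the Discussion says that a finding of no added benefit would be taken as support for withholding medication.

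**Working it through.** **Inputs.** Effect 0.35, correlation r = 0.5, total 260 and two-sided 0.05 come from Statistical methods and determination of sample size; 1:1 allocation, hence n = 130 per arm, comes from Enrolment and randomisation. The ratio of baseline to week-12 SD is not given. Power figures are noncentral-t and rounded unless marked otherwise.

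**Step 1: reproduce 260 (equal SDs, in SD units).**
- Variance of change per person: 2(1 − r) = 2 × 0.5 = 1.00.
- n per arm for 80% power: 2 × (1.960 + 0.842)² × 1.00 / 0.35² = 128.1, so 129 per arm and 258 in total by the normal formula. The t-based answer is 130 per arm, or 260.

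The stated total therefore reproduces for the change contrast at 80% power.

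**Step 2: power with 130 per arm (equal SDs).**
- Change contrast: 0.35 / √1.00 × √(130/2) = 2.82, power 80.3% (normal approximation 80.6%).
- Baseline-adjusted: variance 1 − r² = 0.75; 0.35 / √0.75 × √(130/2) = 3.26, power 90.1% (normal approximation 90.3%).

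A generalised least squares calculation for four visits with complete data gives the same answers. The standard error of the week-12 contrast is 0.1240 with separate baseline means and 0.1074 with a common one (0.35/0.1240 = 2.82; 0.35/0.1074 = 3.26).

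**Step 3: unequal SDs.** Let k be the baseline SD divided by the week-12 SD, with the effect scaled to the week-12 SD. The change variance is k² + 1 − 2rk; the adjusted variance stays at 1 − r² = 0.75.

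| k | Change variance | Power, change | Power, adjusted |
|---|---|---|---|
| 0.6 | 0.76 | 90% | 90% |
| 0.8 | 0.84 | 87% | 90% |
| 1.0 | 1.00 | 80% | 90% |
| 1.2 | 1.24 | 71% | 90% |

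If 0.35 is instead scaled to the SD of change, the change contrast stays at 81% and adjustment gives 85% at k = 0.8 and 81% at k = 0.6 (normal approximation).

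**Step 4: the entry floor.** Assume, because the article gives no such figures, unselected baseline means of 25 to 30, SDs of 6 to 7, r = 0.5 before selection, equal SDs before selection and a cut at 20. Truncating the baseline leaves the regression slope (0.5) and the residual variance (0.75) unchanged. It reduces only the baseline variance, from 1 to between 0.55 and 0.81 across the four combinations.
- The correlation falls to 0.39–0.46.
- Change variance is baseline variance × (1 − 0.5)² + 0.75. At the ends of the range that is 0.55 × 0.25 + 0.75 = 0.89 and 0.81 × 0.25 + 0.75 = 0.95, down from 1.00.
- Effect in unselected SD units: change 82–85%, adjusted 90%.
- Effect in selected week-12 SD units: change 80%, adjusted 86–89%.

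On either scaling the gap narrows to about 5 to 8 points and does not reverse.

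**The case against.** The strongest reply is that nothing here is inconsistent. The outcome is change in MADRS, the contrast is change in MADRS, and 260 participants give a conventional 80% for it. The comparison is unbiased. All of that stands: the point is about efficiency, not validity.

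Second, the article never calls the contrast raw or unadjusted, and never says that each arm has its own baseline mean. A baseline-adjusted repeated-measures model can also report a contrast of change from baseline, and the full protocol or analysis plan may settle the matter. This stands too, and it limits confidence. It does not remove the point, because the article names the contrast, the covariance matrix and the covariates, and on its natural reading baseline is a response with no adjustment.

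Third, the ten-point gap belongs to equal SDs, which the entry floor makes unlikely. That is correct, and the same limit applies to saying that a quarter of the precision is lost (1.00 against 0.75).

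A reader might infer more than the documents support:
- *That the floor of 20 makes the change contrast worse because it lowers the correlation.* It lowers the correlation by shrinking the baseline SD, and the change variance falls with it. Equal-SD figures for low correlations (73% against 87% at 0.4, 66% against 84% at 0.3) therefore do not describe the effect of the floor.
- *That 90% power was intended and has been missed.* An adjusted analysis at 90% does also lead to 260: 2 × (1.960 + 1.282)² × 0.75 / 0.35² = 128.7 per arm, t-based 130. But no primary power is stated, and the same coincidence would fit a plan that meant to adjust all along.

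**Conclusion.** The point holds as one of efficiency. As written, the primary contrast is a valid change-score comparison that uses the baseline less well than a model with a common baseline mean or a baseline covariate. On the article's inputs with equal SDs and complete data, power is about 80% against 90%. The gain almost vanishes if the baseline SD is 0.6 of the week-12 SD and reaches 19 points (71% against 90%) if it is 1.2 times as large. With the entry floor and the assumed baseline distributions, 5 to 8 points is the more likely size. In large samples adjustment is never less precise, so the direction does not depend on the unknown ratio. The 80% is inferred from the sample size, not stated. Confidence is moderate, because separate baseline means are a reading of the text. The change is worth making but is not a condition for a valid trial.

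**What to change.** Before unblinding, replace the sentence on the primary contrast with wording such as: *MADRS at week 12 will be compared between arms in a repeated-measures model with a baseline mean common to both arms (constrained longitudinal model), or with baseline MADRS and baseline-by-visit terms as covariates.* Choose one of the two forms and name it. Use the same model for scaled secondary outcomes that have a baseline value. If the full protocol or analysis plan already specifies this, one confirming sentence is enough.

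The estimand, the between-arm difference in change at week 12, is unchanged. The cost is wording only: no further participants, visits or data.
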